## Abstract

**Background:**

The implementation of physical activity interventions in centre-based childcare services has been recommended to improve child health. This study aims to evaluate the efficacy of scheduling multiple periods of outdoor free play in increasing the time children spend in moderate-to-vigorous physical activity (MVPA) during childcare.

**Methods:**

The study will employ a between group cluster randomised controlled trial design. Fourteen childcare services in the Hunter New England region of New South Wales, Australia, who currently implement a single session of free outdoor play between their core operational hours of 9 am to 3 pm will be recruited into the trial. Childcare services will be randomised to an intervention or a no intervention control group. Childcare services in the intervention group will be supported by an early childhood education specialist to provide three periods of outdoor free play for children between the hours of 9 am to 3 pm. Each period of outdoor free play will be at least 15 min in duration but must equate to their total usual duration of outdoor play. Services in the control group will continue to implement a single period of outdoor play. The primary trial outcome is minutes of time children spend in MVPA whilst in care assessed objectively via accelerometer over 5 days. Outcome assessment will occur at baseline and 3 months post baseline. Generalised Linear Mixed Models (GLMM) under an intention to treat framework will be used to compare differences between groups in the primary trial outcome at follow-up. Sensitivity analysis will be conducted to test assumptions of missing data. Per protocol analysis will be performed using services that implemented the intervention as intended and subgroup analysis undertaken by gender and baseline physical activity levels of children.

**Discussion:**

The study tests a simple ecological intervention that has the potential to increase child physical activity in care.

**Trial registration:**

Australian New Zealand Clinical Trials Registry 12616000347460. Prospectively registered 17th March 2016.

## Background

Inadequate physical activity is associated with the most prevalent causes of mortality and morbidity including obesity, diabetes, cardiovascular disease and some cancers [1]. Physical activity in early childhood has immediate beneficial effects on blood pressure, lipid profile, motor skill and bone development [2–4] with greatest benefit accruing at moderate-to-vigorous intensity [3, 4]. Despite these benefits, research in Australia and internationally has demonstrated that most children aged 2 to 6 years do not engage in physical activity consistent with current national guidelines [5, 6].

A number of characteristics of centre-based childcare services suggest that they represent an ideal setting for interventions to improve physical activity in young children. First, centre-based childcare provides access to a significant proportion of the population aged less than 5 years, often for prolonged periods. For example, approximately 55 % of Australian children aged 0 to 5 years attended some form of centre-based care in 2014 [7]. Second, reviews suggest that young children are not sufficiently active during attendance at centre-based care, necessitating interventions in this setting [8]. Third, childcare service staff believe in the importance of children being physically active as a part of their professional responsibility and are amenable to interventions to support improvements in child activity [9].

Modifying the frequency of outdoor free-play may represent a potentially innovative and effective strategy in improving the physical activity of children attending childcare. Unstructured outdoor free-play (as opposed to structured, staff-guided play) has been consistently associated with greater child physical activity among children in care [10, 11]. However, findings of a randomised trial suggest that increasing the duration of time that children in childcare have available for outdoor free-play may not be effective in improving child physical activity [12]. A likely explanation for this is that extending outdoor free-play time alone does not account for children’s natural physical activity patterns. Children’s activity in care is characterised by short, intense bouts of activity of between 3 and 15 min occurring at the start of outdoor free-play opportunities, followed by extended recovery periods of sedentary behaviour or light activity [13–16]. As such, extending periods of outdoor play alone may not increase child moderate-to-vigorous physical activity (MVPA). However, even if the total duration of outdoor free-play time for children remains constant, scheduling shorter but more frequent opportunities for outdoor free-play may enhance child physical activity by promoting more spontaneous bouts of intense activity (‘activity peaks’) that is characteristic of the first 15 min of outdoor free-play [13].

In this context the aim of this study is to assess the efficacy of scheduling multiple periods of outdoor free-play per day in increasing the time children spend in MVPA during childcare relative to one outdoor play time of the same duration. This manuscript describes the trial methods and trial outcomes of the study.

## Methods

### Design

The study will employ a between group, cluster randomised controlled trial design (see Fig. 1). Fourteen centre-based childcare services with one period of outdoor free-play (of at least 45 min duration) will be randomised to an intervention or control group. Intervention services will change their scheduling of outdoor free-play such that their usual total time for outdoor free-play is broken into multiple separate periods of at least 15 min in duration each with an indoor period of at least 30 min in between. Control services will continue to provide their usual total period of outdoor free-play time across a single continuous period. Intervention efficacy will be determined by comparing differences between groups in the minutes children spend in MVPA per day at childcare. MVPA will be assessed via accelerometer over 5 days at baseline and 3 months later. Approval to conduct the study was obtained from Hunter New England Human Research Ethics Committee (reference number 15/11/18/4.03) and the University of Newcastle Human Research Ethics Committee (reference number H-2016-0088).

**Fig. 1 Fig1:**
[figure not shown]
Flow of participants through each stage

### Participant eligibility and evidence-based recruitment strategy

#### Childcare services

To be eligible to participate in the trial, centre-based childcare services (defined as long day care services or preschools) will be required to have an enrolment of least 25 children aged between 3 to 6 years, be located within the Hunter or New England regions of New South Wales, Australia, and have only one outdoor free-play session occurring between the core operational hours of 9 am to 3 pm. Childcare services catering solely for special needs populations, or those participating in other physical activity interventions will be excluded from participating in the trial.

A list of all childcare services that are licensed to provide care for 3 to 6 year-old children located within the study region will be obtained from the licensing agency. Supervisors of childcare services across the study region will be sent study information prior to telephone contact to assess eligibility and to invite study participation among eligible services. Recruitment will continue until 14 services have consented to participate. Previous studies in childcare utilising this recruitment approach have yielded a childcare service participation rate of 81–84 % [17–19].

#### Children

Active parental consent will be required for study participation. To be eligible for the data collection component of the study, children will be required to be aged 3 to 6 years and attend participating services between 9 am and 3 pm on one or more days in the week of data collection. Children with an intellectual or physical impairment that may impact on their physical activity capacity or prevent them from complying with data collection protocols will be excluded.

To maximise study participation, children will be recruited utilising an evidenced-based strategy recommended for obtaining active parental consent for child participation in school-based research, which will include a mail out of study information and consent forms prior to onsite recruitment, face to face dissemination of information sheets and provision of consent forms to parents during periods of drop-off or pick-up from childcare [20]. Such a recruitment strategy has been utilised in previous trials of interventions for preschool aged children in this setting [21–23].

### Randomisation, allocation and blinding

A statistician with no other involvement in recruitment or data collection will allocate services to either the intervention or control condition in a 1:1 ratio using a computerised random number generator. Randomisation of childcare services will be stratified by the socioeconomic status of the area where the service is located, and on the service type (long day care service or preschool) based on evidence of an association between these factors and the physical activity policies and practices of services [24].

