### Analysis

Minutes of MVPA will be determined using age-specific child-validated equations (cut points) [29]. Generalised Linear Mixed Models (GLMM), to take account of the repeated measures on children (daily measures during baseline and follow-up periods) as well as clustering of individuals within services, will be used under an intention to treat framework to test for a difference in change in minutes of MVPA between groups. The GLMM will include terms for time (baseline and follow-up), group (intervention or control group), and the interaction of time and group, and will control for child gender and total outdoor play time. A sensitivity analysis will be performed using multiple imputation for missing data to assess robustness of the main analysis [37]. Per protocol analysis will be performed using services that implemented the intervention as intended and subgroup analysis undertaken by gender and baseline physical activity levels of children.

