### Sample size and power calculation

The study will approach approximately 500 children from 14 childcare services across the study region. Assuming the standard deviation of MVPA is 2.7 min/h [38] and assuming an intraclass correlation coefficient of 0.1 [39], a sample of 14 children per cluster (assuming a conservative participation rate of approximately 50 and a 20 % loss to follow-up) will provide the study with 80 % power to detect a change of 9.9 min in MVPA. An increase of 10 min of MVPA in children aged 3 to 6 years old has been found to have clinically significant beneficial effects on fat mass and peak bone mass [3, 4].

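### Services are randomised within strata of area socioeconomic status and service type, but the listed primary model contains neither factor, so the analysis does not follow the design

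*Protocol article*

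**What the plan says.** Under Randomisation, allocation and blinding, the protocol article states: "Randomisation of childcare services will be stratified by the socioeconomic status of the area where the service is located". Service type (long day care or preschool) is the second factor. The choice of both is "based on evidence of an association between these factors and the physical activity policies and practices of services".

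The Analysis section sets out a generalised linear mixed model that allows for repeated measures on children "as well as clustering of individuals within services". Its terms are time, group and their interaction, and it "will control for child gender and total outdoor play time". Its purpose is to "test for a difference in change in minutes of MVPA between groups". The Methods paragraph of the abstract describes the same model as one used to "compare differences between groups in the primary trial outcome at follow-up".

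The sample size section gives 80% power for 9.9 min and does not mention stratification.

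**The concern.** When allocation is restricted within strata, the usual practice is to carry the stratifying factors into the primary model. Stratification makes the arms more alike on those factors than simple randomisation would. A model that ignores them counts their variance as between-service error, so the standard error of a comparison of levels is too large for the design used.

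This is more than detail left to an analysis plan. The article fixes a covariate list that names two adjustment variables and omits the two on which services were stratified. With 14 services, a decision to adjust that is taken after the data are seen could visibly move the result, so it should be settled beforehand.

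**Working it through.** **Inputs.** SD 2.7 min/h, ICC 0.1, 14 children per service and 14 services (Sample size and power calculation). Allocation 1:1, so 7 services per arm. A 6 h day (Intervention), so SD = 2.7 × 6 = 16.2 min. Two-sided alpha of 0.05 is assumed because none is stated.

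**1. The plan's own figure.** Variance of a service mean, in units of 16.2²: 0.1 + 0.9/14 = 0.1643. SE of the difference between arms: 16.2 × √(2 × 0.1643/7) = 3.51 min. Normal approximation: 9.9/3.51 − 1.96 = 0.86, so power is 80.5%; the detectable difference at 80% is 2.80 × 3.51 = 9.83 min. The stated 80% at 9.9 min reproduces with no stratification term. On 12 service-level df (14 − 2) the same SE gives 73.6%. That drop comes from the degrees of freedom, not from the strata.

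**2. Follow-up comparison without baseline (abstract wording).** Let the factors explain a share R² of between-service variance. The variance becomes 0.1 × (1 − R²) + 0.9/14. With two binary factors as main effects, df = 14 − 4 = 10.

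| R² (assumed) | SE, min | Power at 9.9 min, noncentral t |
|---|---|---|
| not adjusted | 3.51 | 73.6% (12 df) |
| 0 | 3.51 | 72.0% (10 df) |
| 0.1 | 3.40 | 74.7% (10 df) |
| 0.2 | 3.29 | 77.4% (10 df) |

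Break-even is at R² of about 0.06. If the factors take 3 df, leaving 9, power is 71.0%, 73.6% and 76.4% at R² of 0, 0.1 and 0.2. The unadjusted row takes the test at its nominal SE.

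**3. Difference in change (Analysis section).** Area socioeconomic status and service type do not vary with time, so their main effects drop out of each service's follow-up minus baseline. Take R² = 0.2, half of the remaining service variance persisting between periods, and a child-level correlation of 0.5 (all assumed). The part that does not persist is 0.1 × 0.8 × 0.5 + 0.9 × 0.5/14 = 0.0721, and SE = 16.2 × √(4 × 0.0721/7) = 3.289 min. The stratum variance does not enter, so the SE is the same with or without stratum main effects. At R² = 0.5 it is 2.927 both ways. With 20% loss to follow-up it is 2.8944 without and 2.8941 with them, a difference of under 0.001 min.

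**4. Baseline-adjusted comparison.** Write V for the variance of a service mean and C for its baseline–follow-up covariance. The adjusted variance is V − C²/V, and SE = 16.2 × √(2 × that/7). Under the assumptions of step 3 with R² = 0.2, V = 0.1643 and C = 0.02 + 0.04 + 0.0321 = 0.0921, so SE = 2.906. Removing the stratum variance of 0.02 from both gives V = 0.1443, C = 0.0721 and SE = 2.849, a reduction of 2.0%. The critical t value rises from 2.179 (12 df) to 2.228 (10 df), or 2.3%, which offsets it.

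**The case against.** The strongest reply is that the Analysis section defines the test, and the test is on change. Steps 3 and 4 bear this out: stratum main effects leave the time-by-group term practically untouched, and even a baseline-adjusted model gains little. A fixed imbalance between arms from odd-sized strata cancels from change in the same way. This part of the objection stands, and it confines the precision argument to the abstract's follow-up wording or to factors that predict change.

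Three further points also stand. The cited association is with services' policies and practices, not with children's MVPA, so no particular R² is supported. Total outdoor play time, itself a service practice, is already in the model and may absorb part of any effect. The article also does not say why stratification was wanted; balance between arms is as natural a purpose as precision.

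A reader might nevertheless infer a large loss of power in the primary test, since shares of 40% or 60% in step 2 would give 83.2% or 89.0%. The document does not support this. Those figures apply only to a follow-up comparison that ignores baseline, and nothing in the text suggests shares of that size.

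The objection does not remove the mismatch itself: the article names its covariates, leaves out the factors used at randomisation and gives no reason.

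**Conclusion.** The analysis as listed does not follow the stratified design. The consequence is modest and in the conservative direction. For a follow-up comparison, power at 9.9 min moves from 73.6% to about 75–77% if the factors explain 10–20% of between-service variance, and down to 72.0% if they explain none. For the time-by-group test, nothing material changes unless the factors also predict change in MVPA, which the document does not suggest. These results rest on two-sided alpha of 0.05, two-level socioeconomic status, uncrossed factors, the assumed R² values and, in steps 3 and 4, the assumed correlations over time.

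A reader might also infer that the sample size is undermined. It is not: the 80% reproduces without any credit for stratification.

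**What to change.** State which contrast is primary, so that the abstract and the Analysis section agree. Then prespecify area socioeconomic status and service type, coded as at randomisation, in the form that acts on that contrast. In a baseline-adjusted or constrained-baseline model, this means main effects. If the time-by-group model is kept, it means factor-by-time terms, since main effects alone would do nothing there. If the factors are to be left out, say so and give the reason.

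The cost is a line in the analysis plan, as both factors are known at randomisation. The statistical cost is about 2 of 12 service-level df if socioeconomic status is binary and the factors are not crossed. It is 3 with three socioeconomic levels or four crossed strata, and more with finer coding, so a sparse coding is preferable with 14 services.

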### Intervention

The intervention will seek to create a childcare environment more supportive of child physical activity by scheduling multiple opportunities for outdoor free-play in a way which is consistent with children’s developing fitness levels [25] and natural physical activity patterns [10, 13, 26]. Specifically, within a 6 h day (9 am to 3 pm) the intervention will divide their usual total time of outdoor free-play for children across three periods of at least 15 min duration.

Three periods of outdoor free-play was selected as: i) research has demonstrated repeated spikes in activity across the day in childcare coinciding with scheduled breaks [13, 16]; and ii) that the start of such breaks stimulate between 3 and 15 min of intense activity, sufficient to achieve an additional 10 min MVPA [27]. The minimum period of outdoor free-play of 15 min was selected given evidence that MVPA often attenuates after this period [13]. Furthermore, services will be required to schedule at least 30 min of indoor time (structured or unstructured play) between periods of outdoor free-play, based on evidence that children may be more likely to be moderate-to-vigorously physically active following prolonged indoor periods [28]. Immediately following baseline data collection, intervention services will be supported by a member of the research team and an early childhood education specialist to implement the intervention. This support will include written materials and at least two site visits and two telephone support calls prior to follow-up data collection to re-orient their operations to incorporate the scheduling change. No other intervention support will be provided to children, childcare service staff or parents.

### Control

Services allocated to the control group will schedule their usual single period of outdoor free-play for children across the day. Control services will also be instructed to continue the one outdoor free-play period of the same duration (except during inclement weather) across the study period.

### Data collection and measures

Data will be collected at baseline and approximately 3 months post baseline.

#### Primary trial outcome—minutes spent in moderate-to-vigorous physical activity in care

The primary trial outcome is the number of minutes children spend in MVPA during the core hours of service operation (9 am to 3 pm). MVPA will be objectively assessed using an Actigraph GT3X+ accelerometer using recommended cut-points [29]. The Actigraph accelerometer has established utility, validity and reliability and is the current gold standard for assessment of activity in children aged 3 to 6 years old [30].

Accelerometers will be worn by children during the core operational hours of childcare (9 am to 3 pm). Two data collectors, not blinded to allocation at follow-up, will attend services to fit and collect accelerometers using a standard protocol [29]. Accelerometers will be placed above the iliac crest at the hip of the child using a clip or band. Accelerometer data will be collected on every day of 1 week (5 days in total) of the data collection period at baseline and follow-up. Children will wear the accelerometer each day (up to 5 days) that they attend care. The accelerometer will be fitted as the children arrive at the childcare service and removed at 3 pm or earlier when the child departs the service. Despite evidence to suggest that increases in child activity at childcare do not result in decreased activity at home [31], at baseline and follow-up, consent will be sought for children to wear accelerometers during ‘out of care’ hours also to assess potential compensatory effects.

#### Secondary trial outcomes

Secondary trial outcomes include total child activity (counts per minute collected in 5 s epochs) in care [32] and percent of time children spend in MVPA adjusted for wear time, assessed via accelerometer. Additionally, as a potential adverse effect of the intervention, during interviews with childcare services, the number of injuries requiring documentation will be assessed using items taken from previous childcare physical activity studies [21].

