#### Service characteristics

During a telephone interview with supervisors of participating childcare services the following service characteristics will be assessed: postcode of locality (to assess the socioeconomic status of the area) [35]; number of years in operation; total number of 3 to 6 year-old children enrolled; number of staff; staff qualifications; and service governance (Department of Education service or privately owned). Such items were drawn from previous studies [17, 24].

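### Injuries, the only outcome labelled a potential harm, are a number given in interview by staff who know their arm, with no stated use of the injury record and no counting window

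*Protocol article*

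**What the plan says.** Under Secondary trial outcomes, the protocol article introduces injuries as a possible adverse effect of the intervention, and states that "during interviews with childcare services, the number of injuries requiring documentation will be assessed using items taken from previous childcare physical activity studies". This fixes both the source (an interview with the service) and what is captured (a number). No other outcome is labelled an adverse effect. The section does not mention the injury record, a counting period or a denominator.

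The article does not say who answers the injury question. The nearest statement concerns other data, under Service characteristics: "During a telephone interview with supervisors of participating childcare services the following service characteristics will be assessed". The items listed there include the "total number of 3 to 6 year-old children enrolled", so one possible denominator is already collected.

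On knowledge of allocation, the Intervention section says that "intervention services will be supported by a member of the research team and an early childhood education specialist to implement the intervention", and the Control section says that "Control services will also be instructed to continue the one outdoor free-play period of the same duration". Data collection and measures places data collection at baseline and about 3 months later, without naming injuries.

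**The concern.** The primary outcome is measured by accelerometer. The one labelled harm rests on what the service says when asked, and in the intervention arm the service is reporting on a change that it made itself. If willingness or effort to report differs by arm, the injury comparison is distorted in a way that randomisation does not correct. Under-reporting in the intervention arm would give false reassurance on safety, while extra vigilance there would suggest a harm that does not exist.

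The stated method also passes over a better source. The outcome is limited to injuries that have to be documented, so a written record made at the time should already exist.

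**Working it through.** The article gives no design figure for injuries. Its only one, a detectable difference of 9.9 min under Sample size and power calculation, concerns MVPA and has no bearing here. All injury figures below therefore rest on stated assumptions.

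**1. Knowledge of allocation.** The article calls only its data collectors unblinded. For service staff the conclusion follows from the Intervention and Control sections: a service cannot rearrange its day into three outdoor periods, or be told to keep one, without knowing which it does.

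**2. Effect of differential reporting.** Observed ratio = true ratio × (fraction reported in intervention ÷ fraction reported in control). The fractions are assumptions.

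| Reported: intervention / control | True ratio 1.0 seen as | True ratio 1.5 seen as |
|---|---|---|
| 80 % / 80 % | 1.00 | 1.50 |
| 90 % / 100 % | 0.90 | 1.35 |
| 80 % / 100 % | 0.80 | 1.20 |
| 70 % / 100 % | 0.70 | 1.05 |
| 100 % / 80 % | 1.25 | 1.88 |

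Under-reporting that is equal in both arms leaves the ratio unchanged. Only a difference between arms matters, and it acts in full.

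**3. Service size (secondary).** Eligible services must "have an enrolment of least 25 children aged between 3 to 6 years", with no upper limit. Randomisation is stratified by area socioeconomic status and service type, not by size. About 500 children are to be approached in 14 services: 500 / 14 = 35.7, about 36 each. Assume that this approximates enrolment, that sizes are uniform from 25 to an upper limit U, and that injury rates are identical everywhere.

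- Variance per service = (U − 25)² / 12.
- SD of the difference in arm totals, 7 v 7 services = √(14 × variance).
- For a mean of 35.7, U = 46.4: variance 38.3; SD √(14 × 38.3) = 23.1; arm total 7 × 35.7 = 250; 23.1 / 250 = 0.093; × 1.96 = about ±18 %.
- For U = 50: variance 52.1; SD 27.0; arm total 262.5; ratio 0.103; about ±20 %.
- For U = 75: variance 208.3; SD 54.0; arm total 350; ratio 0.154; about ±30 %. This implies 50 children per service, which fits the article's 36 less well.

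This is a chance spread centred on no difference.

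**4. What a denominator buys.** In a simulation of 7 v 7 services, sizes had a nominal mean of 36 (values below 25 raised to 25), and counts were Poisson at an assumed 0.3 injuries per child per 3 months, with no variation in rate between services of the same arm. Power of a service-level t-test for a true rate ratio of 1.5 was:

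- all services the same size: 72 % for raw counts and 72 % per enrolled child;
- size CV 0.25: 48 % and 70 %;
- size CV 0.5: 28 % and 69 %.

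At CV 0.5, the false-positive rate of that test on raw counts stayed at about 5 %. It reached 26 % only when pooled arm totals were compared as Poisson counts.

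**The case against.** The strongest reply is that an interview need not mean memory. The items come from earlier childcare studies that are not at hand. They may ask the service to consult its records and may fix a period, and the restriction to documented injuries points that way. This stands in part: recall without records is not stated and should not be asserted. But the article names the interview as the source and says nothing of the record, so the weaker reading is left open for the one labelled harm.

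A second reply concerns size. A reader might infer that raw arm totals will be compared and that large services will bias the result. The documents do not support this. The Analysis section specifies a model for minutes of MVPA only, and the analysis of injuries may sit in documents not shown. Enrolment is collected, so a rate can be formed. Size imbalance under randomisation costs precision and does not favour either arm. This reply stands, and the denominator is secondary for that reason.

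A third reply is that counts at baseline and follow-up would allow a comparison of change. If injuries are asked about at both times, much of the size effect would cancel, as would any reporting habit that is stable over time. A shift in reporting that begins once services know their arm would not cancel.

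Finally, reading from records does not blind anyone. Staff who know their arm still decide which injuries to write down. This also stands: the remedy reduces differential reporting but does not abolish it.

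**Conclusion.** The point holds for the source of the count. The only outcome labelled a potential adverse effect is a number reported in interview by respondents who necessarily know their allocation, with no stated use of the injury record and no counting window. The count should come from the record, because that source is less open to differential reporting and should already exist.

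The size of the distortion cannot be fixed from the documents. The move from a true 1.5 to an observed 1.2 rests wholly on assumed reporting of 80 % and 100 %. The effect of service size, about ±18 % to ±20 % in arm totals, assumes about 36 enrolled children per service and a uniform spread; it is noise, not bias. The documents do not support the stronger claims that staff will answer from memory, or that service size will produce a false safety signal. For a secondary outcome this is a change worth making, not a flaw that threatens the trial's main result.

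**What to change.** Reword the interview item so that the service reads or copies the number from its own injury records, with dates, for two fixed windows of equal length that are the same in both arms: one ending at baseline, and one from baseline to follow-up (about 3 months each). Report injuries per enrolled child, using the enrolment of 3 to 6 year-olds that is already collected and counting injuries in the same age group. Compare the arms with allowance for clustering by service.

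The cost is a revised item and slightly more effort for supervisors. It needs no new assessor and no change to the sample size or the intervention. Attendance-days would be a finer denominator, but they are not among the items listed and would be new data collection. The report should state the remaining limitation: the threshold for documenting an injury could still differ by arm.
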